#### GAIN Aim 3 Eligibility (Evaluate the Impact of a Semiquantitative POC NAT on Time to Virologic Suppression Among People Living With HIV in a Clinical Setting and Assess Acceptability of Viral Load Testing in a Community Setting Among People Living With HIV)

Participants were recruited for Aim 3 if they were at least 18 years old, proficient in English, living with HIV, and seeking STI testing at the Center or HIV care at the Madison Clinic or MOD Clinic. These patients were only eligible to participate in the study once.

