### Study Procedures

#### GAIN Participants Seeking HIV Testing at Both Sites and Participants With HIV at the Center

Enrollment began in January 2022 for patients seeking HIV testing and March 2022 for people with HIV to give study staff time to achieve proficiency in one set of study procedures before adding another group. Participants signed a bi-directional release of information allowing the study team to obtain follow-up data for the year following the study visit and document research test results in the patient EMR. Study staff then completed a linking survey on a secure server including patient identifiable information and the study record of the participant. Then the participant completed a brief study visit survey in REDCap (Research Electronic Data Capture; Vanderbilt University) with demographic questions linked only to the participant’s study record.

After completing study paperwork, study staff collected fingerstick whole blood for the POC NAT. For participants seeking HIV testing, we used the SAMBA Qual, which provides a negative or positive result. European Union–approved materials state that the SAMBA Qual can detect as low as 400 copies of virus as early as 10 days after exposure [42,45]. For participants with HIV, we used the SAMBA Semi-Q, which provides a result of greater or less than 1000 copies per milliliter of blood [22]. Both versions of the test return a result in approximately 2 hours, and neither test is FDA approved. In June 2023, after a series of false-positive test results, we added a second SAMBA Qual using venipuncture whole blood for the participants seeking HIV testing at the Center to provide an additional backup to the fingerstick test.

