#### GAIN Participants With HIV in the Madison Clinic RCT

Participants in the RCT signed a release of information and completed the linking survey and study visit survey as described above [36]. Then participants in this group were randomized by 1:1, variable-block-size randomization to either receive either the clinic standard of care or the standard of care plus the SAMBA Semi-Q and tailored counseling.

Beginning in April 2023, study staff also performed venipuncture for participants in both arms and drew a 10 mL EDTA tube for a study laboratory NAT and, if possible, for the convenience of the participant, any additional tubes for clinical purposes. This change was made to ensure that all persons had an FDA-approved NAT that could be used as the primary way to guide clinical decision-making.

For participants in both arms, study staff obtained follow-up data from ITHS to monitor patient outcomes for 1 year after the study visit. Viral loads were obtained from the standard-of-care group at the time of the study visit and through up to 1 year of follow-up so that time to virologic suppression could be compared between the 2 arms.

For participants randomized to the intervention arm, study staff also conducted a fingerstick and initiated the SAMBA Semi-Q. After the study procedures were completed, study staff connected the participant with their care team to complete their clinic visit. When the SAMBA Semi-Q result was ready, study staff delivered the result to the participant’s physician. When participants were still in the clinic, the physician delivered the result along with the brief adherence counseling intervention developed for the study in collaboration with clinic providers, the process for which has already been described (Multimedia Appendices 1 and 2) [36]. For participants who had left the clinic, the physician followed up with the patient either via phone or by EMR message, whichever was considered most appropriate. For each participant randomized to the POC NAT arm, the physician reported to the research study whether they discussed the POC NAT result with the participant in person, via phone, or not at all. SAMBA Semi-Q and research laboratory NAT results were manually entered into the EMR by the research team.

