Characteristics	Baseline visits by patients at Madison Clinic (Jan 2019-Dec 2021)			GAIN^a^ study visits (Jan 2022-Aug 2024)
	Patients with first reactive HIV result	Patients with detectable HIV viral load	Total patients	Participants with HIV
Total, n (%)	146 (22.2)	511 (77.8)	657 (100)	194 (100)
Age (years), median (IQR)	34 (28‐47)	43 (32‐52)	41 (31‐51)	44.5 (35-57)
Gender, n (%)				
Cisgender man	117 (80.1)	406 (79.5)	523 (79.6)	144 (74.2)
Cisgender woman	29 (19.9)	104 (20.4)	133 (20.2)	19 (9.8)
Transgender man	0 (0.0)	0 (0.0)	0 (0.0)	0 (0.0)
Transgender woman	0 (0.0)	0 (0.0)	0 (0.0)	10 (5.2)
Nonbinary or genderqueer (AMAB)^b^	0 (0.0)	0 (0.0)	0 (0.0)	15 (7.7)
Nonbinary or genderqueer (AFAB)^c^	0 (0.0)	0 (0.0)	0 (0.0)	0 (0.0)
Nonbinary or genderqueer (unknown sex at birth)	0 (0.0)	1 (0.2)	1 (0.2)	0 (0.0)
Another gender identity	0 (0.0)	0 (0.0)	0 (0.0)	6 (3.1)
Missing	0 (0.0)	0 (0.0)	0 (0.0)	0 (0.0)
Race or ethnicity, n (%)				
American Indian or Alaska Native	0 (0)	14 (2.7)	14 (2.1)	3 (1.6)
Asian	10 (6.8)	20 (3.9)	30 (4.6)	4 (2.1)
Black or African American	43 (29.5)	152 (29.7)	195 (29.7)	53 (27.3)
Hispanic or Latinx^d^	12 (8.2)	21 (4.1)	33 (5.0)	27 (13.9)
Native Hawaiian or Other Pacific Islander	1 (0.7)	8 (1.6)	9 (1.4)	5 (2.6)
White	56 (38.4)	239 (46.8)	295 (44.9)	84 (43.3)
Multiracial^e^	4 (2.7)	4 (0.8)	8 (1.2)	17 (8.8)
Missing or no response	20 (13.7)	20 (3.9)	40 (6.1)	1 (0.5)
Insurance, n (%)				
Public insurance	55 (37.7)	325 (63.6)	380 (29.8)	162 (83.5)
Private insurance	61 (41.8)	135 (26.4)	196 (57.8)	28 (14.4)
Another insurance	12 (8.2)	17 (3.3)	29 (4.4)	1 (0.5)
Missing	18 (12.3)	34 (6.7)	52 (7.9)	3 (1.6)
ART^f^ use, n (%)				
Never	ND^g^	ND	ND	38 (19.6)
Previously	ND	ND	ND	19 (29.4)
Currently	ND	ND	ND	134 (69.1)
missing	ND	ND	ND	3 (1.6)
Laboratory viral load, n (%)^h^				
Detectable (≥40 copies)	N/A^i^	N/A	N/A	63 (32.5)
Undetectable (<40 copies)	N/A	N/A	N/A	113 (58.2)
Laboratory viral load not done	N/A	N/A	N/A	18 (9.3)^j^
Randomization arm, n (%)				
Standard of care	N/A	N/A	N/A	97 (50)
Point-of-care NAT^k^	N/A	N/A	N/A	97 (50)

a GAIN: Greater Access and Impact through Point-of-Care Nucleic Acid Test.

b AMAB: assigned male at birth.

c AFAB: assigned female at birth.

d Participants who selected Latinx and any other race were categorized as Latinx.

e Participants who selected any 2 or more races but not Latinx were categorized as multiracial.

f ART: antiretroviral therapy

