Test results data from Aim 1 participants at both the Center and Madison Clinic will contribute to a performance assessment of the SAMBA Qual, anticipated in 2027. For this analysis, we will calculate the overall specificity and sensitivity of the SAMBA II Qual whole blood test across all tested samples and at HIV-1 RNA thresholds of detectable (>40), 200, 400, 1000, 2000, and 3000 copies/mL. SAMBA performance will be compared to laboratory RNA test results. We hypothesize that the sensitivity and specificity of the SAMBA II Qual will be similar to those of laboratory-based pooled NAT.

Test results and longitudinal follow-up from Aim 3 participants at Madison Clinic will contribute to a survival analysis of time to undetectable viral load, as well as a performance assessment of the SAMBA Semi-Q, anticipated in 2026. We will report the limit of detection using the plasma HIV RNA level as the gold standard, and the agreement (kappa) between SAMBA and plasma HIV RNA levels, dichotomized at 1000 copies/mL and within the range of 1000 copies/mL ± 0.3 log.

For the survival analysis, we will report the time to an undetectable viral load by study arm. We calculated a sample size of 106 per arm, assuming a baseline of 40% of participants with an undetectable viral load, to detect a 20% increase in the proportion of participants with an undetectable viral among people with HIV at Madison Clinic, assuming a 20% loss to follow-up. We hypothesize that the SAMBA Semi-Q will have high agreement with the laboratory-based RNA testing, and that time to virologic suppression will be shorter among participants randomized to the POC NAT-tailored intervention compared with standard of care.

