Data from Aim 4 will contribute to a paper on the acceptability of POC NAT among persons testing for HIV, anticipated in 2026 (Table 7). Another paper will address the acceptability of POC NAT among people with HIV using both qualitative data from interviews and participant survey responses, anticipated in 2026. Another paper using data collected as part of Aim 4 activities will explore HIV testing preferences using both the acceptability survey and interview data. We will use a convergent parallel mixed methods design for integration of qualitative and quantitative data. For the interview sample size, we planned to conduct 20 interviews each among the HIV testing group and people with HIV, or until saturation of themes. For surveys, a sample size of 100 HIV testing participants and 100 people with HIV was determined based on feasibility, the literature, and consultation with a choice-modeling expert. We hypothesize that more than 80% of participants surveyed will report a positive experience with POC NAT and that SAMBA implementation will be acceptable in community- and clinic-based settings. However, we hypothesize that the 2-hour TAT will be a limitation to the feasible implementation of POC NAT and that the semiquantitative nature of the test and the limit of detection of 1000 copies/mL may cause some hesitation in the use of the SAMBA Semi-Q.

**Table 7. T7:** Planned publication topics, analyses, and timelines.

Anticipated publication topics	Contributing aims and sites	Planned analysis	Target sample size	Attained sample size	Anticipated publication date
Performance of SAMBA Qual for HIV Testing	Aim 1, Seattle’s LGBTQ+ Center and Madison Clinic	Laboratory and POC^a^ NAT^b^ concordance	850 study visits	550 study visits	2027
Impact of POC NAT on time to undetectable viral load and SAMBA Semi-Q performance	Aim 3, Madison Clinic	Survival analysis, laboratory, and POC NAT concordance	212 study visits with up to 1-year longitudinal follow-up	194 study visits	2026
Acceptability of POC NAT among persons testing for HIV	Aim 4 interviews, Seattle’s LGBTQ+ Center and Madison Clinic	Qualitative	20 or until saturation of themes	21 interviews	2026
HIV testing preferences	Aim 4 interviews and surveys, Seattle’s LGBTQ+ Center and Madison Clinic	Qualitative, discrete choice analysis	20 or until saturation of themes, 100 surveys	21 interviews, 143 surveys	2026

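### The planned limit of detection for SAMBA Semi-Q cannot be usefully estimated from one above/below-1000 reading in about 31 viremic participants; the data show only where the reading switches

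*Protocol article*

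**What the plan says.** In the Results section, the paragraph on Aim 3 analyses names two performance outputs for SAMBA Semi-Q. One is kappa agreement at 1000 copies/mL and within ±0.3 log of it. The other is separate: "We will report the limit of detection using the plasma HIV RNA level as the gold standard". The same paragraph gives the data source: "Test results and longitudinal follow-up from Aim 3 participants at Madison Clinic will contribute to a survival analysis", with the Semi-Q assessment drawing on the same participants. No detection probability is attached to the limit.

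The design facts that bear on it are these:

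- **Output of the test** (procedures for testing participants and for Center participants with HIV): for people with HIV, "we used the SAMBA Semi-Q, which provides a result of greater or less than 1000 copies per milliliter of blood".
- **Who is tested** (Madison Clinic RCT procedures): "For participants randomized to the intervention arm, study staff also conducted a fingerstick and initiated the SAMBA Semi-Q". The standard-of-care arm has no Semi-Q reading.
- **How often** (Aim 3 eligibility): "These patients were only eligible to participate in the study once".
- **How many** (Table 4): 97 participants in the point-of-care arm. Over both arms, 63 of 194 fall in the row "Detectable (≥40 copies" and 18 have no laboratory viral load.

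Later in Results, among the Aim 4 hypotheses, the article says that "the limit of detection of 1000 copies/mL may cause some hesitation in the use of the SAMBA Semi-Q".

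**The concern.** A limit of detection is the concentration at which an assay finds the target with a stated probability. A reading below 1000 on this test does not say whether virus was detected; it says only that the result fell on the low side of a preset reporting cut-off. Estimating a detection limit takes repeated tests at known concentrations, or many specimens near the threshold. The article describes one reading per person over whatever viral loads the participants happened to have.

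The Aim 4 sentence adds to the difficulty. It treats the 1000 copies/mL cut-off as the limit of detection and as already known, whereas the Aim 3 paragraph plans to report a limit of detection measured against plasma RNA.

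What is at stake is one named output of the Aim 3 performance paper. A figure published under that name, for a fingerstick test without FDA approval, could be taken as a property of the assay. It would in fact depend mainly on where a handful of viral loads near 1000 copies/mL happened to fall.

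**Working it through.** **1. Number of informative pairs.** The article's own figure reproduces: 63/194 = 32.5% viremic. Viremia is not given by arm, so the expected number in the tested arm is 97 × 63/194 = 31.5. If 63 viremic participants are split at random between two arms of 97, the hypergeometric 95% range is 25 to 38. The calculations below use 31.

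**2. Number near the threshold.** 1000 copies/mL ± 0.3 log runs from 10^2.7 = 501 to 10^3.3 = 1,995 copies/mL. The spread of viral loads is not in the document. Assume log10 viral load is uniform from 1.6 (40 copies/mL) to 5 or 6. Then 31 × 0.6/3.4 = 5.5 or 31 × 0.6/4.4 = 4.2 participants fall in that band. Over the wider set of distributions in step 4 the figure is about 3 to 6.

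**3. What those data say about a threshold.** Model: P(reading above 1000) = Φ[(log10 RNA − 3)/s], with the 50% point at 1000 copies/mL. The steepness s is also an assumption, taken as 0.15 to 0.25 log10. The 95% point is 10^(3 + 1.645s), which is about 1,765 copies/mL at s = 0.15 and about 2,580 at s = 0.25. Each simulated trial has 31 single readings and viral loads as in step 2.

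| Quantity | Result over these settings |
|---|---|
| Trials with complete separation (every above-1000 reading at a higher plasma RNA than every below-1000 reading), so probit has no finite slope | about 31–73% |
| Median width of the 95% profile-likelihood interval, 95% point | about 4- to 9-fold |
| Median width of the 95% profile-likelihood interval, 50% switch point | about 2- to 3-fold |

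**4. Sensitivity.** The assumptions were widened to s = 0.1–0.3, with log10 viral load either uniform from 1.6 to 6 or normal with SD 1.2 and mean 3.5 or 4.3.

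| Viremic pairs | Median 95% interval width, 95% point |
|---|---|
| 25 | about 4- to 17-fold |
| 31 | about 3.5- to 11-fold |
| 38 | about 3- to 9-fold |
| 63 (as if both arms had been tested) | about 2- to 6-fold |

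At 31 pairs, complete separation occurred in about 23–94% of these trials. No setting gave a tight estimate of the 95% point.

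**The case against.** The strongest reply has four parts.

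*The data do contain threshold information.* A reader might infer from the separation rates that the threshold is undefined, or that no limit can be computed at all. That does not follow. Separation makes the probit slope infinite, but the data then bracket the switch point between the highest viral load read below 1000 and the lowest read above it. The profile-likelihood interval was bounded in almost every simulated trial, and under the step 3 assumptions it was narrower in the separated trials than overall. The document also names no probit model. This part stands: the problem is an estimate too imprecise to use and wrongly labelled, not one that does not exist.

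*The 95% definition is brought in from outside.* The article gives no detection probability, and a condensed article may leave that to a fuller plan. Its absence is not the complaint. If the 50% switch point is meant, an interval about 2- to 3-fold wide has descriptive value. Even so, that quantity describes behaviour around a preset cut-off and should not be called a limit of detection.

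*The sizes rest on assumptions.* This stands too. The viral-load spread, the steepness and the split of viremia by arm are not in the document. The direction held over every combination tried.

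*Agreement at 1000 copies/mL is already planned, and Table 7 lists only concordance and the survival analysis.* True. It makes the change smaller, but the text still commits to the limit of detection as a separate output.

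**Conclusion.** The point holds as a mismatch between a named output and the design stated in the same article. A binary reading at a preset cut-off, taken once per person in one arm with about 31 viremic pairs, locates where the reading switches relative to plasma RNA. It does not give a usable analytical limit of detection. Under the stated assumptions the 95% point would typically carry an interval about 4- to 9-fold wide, and the 50% switch point one about 2- to 3-fold wide.

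The design facts come from the document. The sizes depend on the assumed viral-load spread (log10 uniform from 1.6 to 5–6), the assumed steepness (SD 0.15–0.25 log10) and an even split of viremia between arms.

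A reader might also infer that the kappa at 1000 copies/mL or the time-to-suppression comparison is compromised. Neither uses the limit of detection, so neither is affected. The wording in the Aim 4 hypothesis is loose terminology with no analytic consequence of its own.

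**What to change.** In the Aim 3 analysis paragraph, replace the limit-of-detection output with:

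- positive agreement among participants with plasma RNA of 1000 copies/mL or more, and negative agreement among those below 1000, each with an exact 95% confidence interval;
- the proportion reading above 1000 in each plasma RNA stratum, for example <40, 40–499, 500–999, 1000–1999, 2000–9999 and ≥10,000 copies/mL.

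This is close to what the article already plans for the SAMBA Qual, which is assessed at a series of RNA thresholds. If a threshold is still wanted, report it as the observed switch point with a likelihood-based interval, and do not call it a limit of detection. In the Aim 4 hypothesis, call 1000 copies/mL the reporting cut-off.

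The cost is a change of wording and a simple table from data in hand. The paper gives up a limit-of-detection claim.

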## Methods

### Description of the Protocol for the GAIN Study

The GAIN study consists of 4 study aims, enrolling study populations at 2 sites (Figure 1). Baseline data obtained from the preenrollment period among nonstudy participants at both sites provided a retrospective preimplementation dataset for comparison with the study participants. Aim 1 evaluated the implementation of the SAMBA II HIV-1 Qual (SAMBA Qual, Diagnostics for the Real World Ltd, Morgan Hill, California, United States) among HIV testing programs via a longitudinal, prospective study of persons without HIV seeking HIV testing, nonoccupational postexposure prophylaxis (nPEP), and PrEP care at Seattle’s LGBTQ+ Center (the Center) and Madison Clinic. Aim 2 evaluated the sensitivity, specificity, and clinical outcomes using the data collected as a part of Aim 1. Aim 3 evaluated the impact of the SAMBA II HIV-1 Semiquantitative (SAMBA Semi-Q, Diagnostics for the Real World Ltd, Morgan Hill, California, United States) on time to virologic suppression via a randomized controlled trial (RCT; NCT04880200), for people with HIV at Madison Clinic and assessed the acceptability of viral load testing outside of a clinical setting among any people with HIV seeking sexually transmitted infection (STI) testing at the Center. Aim 4 examined acceptability and feasibility of the POC NAT using surveys and in-depth interviews with participants and care providers. Finally, a systems engineering component of the study conducted time and motion observations of patient flow through Madison Clinic at one time point preimplementation and 2 time points postimplementation, informed study implementation, and provided information about the impact of POC testing on clinic flow.

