#### Time and Motion Eligibility

Any Madison Clinic or MOD Clinic patient was eligible to be observed by study staff during their clinic visit to assess pre- and post-study implementation clinic flow.

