#### GAIN Time and Motion Observations

Time-and-motion studies were conducted at three times: February-July 2021 before study enrollment began to inform study implementation, March-April 2023 for a post-COVID pandemic repeat assessment (during a regulatory study pause in enrollment), and November 2023 to October 2024 during study enrollment to assess the impact of the POC NAT on clinic flow [37]. Patients were observed by study staff from the time they arrived in the waiting room until they departed the clinic, with staff noting the type of visit and the time of each subsequent segment of the patient visit (eg, front desk check-in, waiting room time, and time the patient spent with each provider type). The final time-and-motion dataset conducted during study enrollment also noted participant time spent on research procedures. That final dataset evaluating the impact of POC NAT implementation will be reported elsewhere.

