	Participants seeking HIV and STI^c^ testing, n (%)	Participants with HIV, n (%)	Participants seeking HIV and STI testing, nPEP^d^, and PrEP^e^, n (%)	Participants with HIV, n (%)	
Total study visits^f^	228 (47)	6 (86)	25 (58)	161 (83)	420 (57)
Survey invitations sent^g^	198 (86.8)	4 (66.7)	21 (84)	77 (47.8)	300 (71.4)
Surveys completed	133 (67.2)	3 (75)	10 (47.6)	47 (61)	193 (64.3)
Interviews completed	16 (12)^h^	1 (33.3)	5 (50)	19 (40.4)	41 (21.2)

a GAIN: Greater Access and Impact through Point-of-Care Nucleic Acid Test.

b LGBTQ+: lesbian, gay, bisexual, transgender, queer, and others.

c STI: sexually transmitted infection.

d nPEP: nonoccupational postexposure prophylaxis.

e PrEP: pre-exposure prophylaxis.

f Includes study visits during which participation in the acceptability survey was being offered

g Includes participants who were offered, agreed, and were eligible to be sent the acceptability survey at their study visit.

h Study staff stopped offering enrollment to all participants after thematic saturation was attained; therefore, not all eligible participants were invited.

Time-and-motion observations were made in 2021 for 25 total patients at Madison Clinic, 13 of whom were from the MOD Clinic (Table 6). We found that the median clinic visit time was 73 (IQR 54‐92) minutes. An additional set of time-and-motion observations, made in 2023 during a pause in study enrollment, included 22 total patients at Madison Clinic (10 of whom were from the MOD Clinic) and revealed a median clinic visit time of 64 (IQR 45‐88) minutes. This demonstrated that most patient visits were shorter than the amount of time the POC NAT used for the study would take to return a result (120 min). This finding led the study team to develop a protocol prioritizing recruitment of participants before their regular clinic visit to initiate the SAMBA test as soon as possible.

**Table 6. T6:** Total time observed in clinic (minutes), including waiting room time, during 1 observation period preenrollment (2021) and 1 period while enrollment was paused (2023).

Year and statistics	MOD^a^ Clinic	Madison Clinic	Total
2021, n	13	12	25
Range	46-301	19-155	19-301
Mean (SD)	93.5 (66.9)	66.8 (36.2)	80.7 (55.0)
Median (IQR)	74 (55-97)	64 (42-85)	73 (54-92)
2023, n	10	12	22
Range	32‐185	45‐95	32‐185
Mean (SD)	75.2 (43.6)	65.3 (17.2)	69.8 (31.6)
Median (IQR)	68 (61-74)	61 (51-80)	64 (45-88)

a MOD: Moderate Needs.

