Acceptability of POC NAT among patients with HIV	Aim 4 interviews and surveys, Madison Clinic and Seattle’s LGBTQ+ Center	Qualitative and descriptive statistics	20 or until saturation of themes,100 surveys	20 interviews, 50 surveys	2026
Time and motion	Patients at Madison Clinic and MOD Clinic	Rank-sum tests and flow analysis	10 visits per clinic per observation period	47 patient visits	2026

a POC: point-of-care.

b NAT: nucleic acid test.

Data collected as part of the time-and-motion component of the study will be the subject of a paper anticipated in 2026. We calculated a sample size of 20 participants during each observation period, assuming a mean visit duration without SAMBA of 66 minutes, an SD of 29, α=.05, 80% power, and that 50% of participants would be randomized to receive SAMBA Semi-Q testing. We hypothesize that the average clinic visit will be less than the 2-hour TAT of the POC NAT and that the impact of study procedures on clinic flow will be minimal.

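### The time-and-motion power statement can apply only to the third observation period, and 10 versus 10 visits there cannot show that the impact on clinic flow is minimal.

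*Protocol article*

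**What the plan says.** The sample-size sentence near the end of Results reads "We calculated a sample size of 20 participants during each observation period, assuming a mean visit duration without SAMBA of 66 minutes". Its other inputs are an SD of 29, alpha .05, 80% power, and 50% of participants randomized to SAMBA Semi-Q. The next sentence hypothesizes that the average visit will be shorter than the 2-hour turnaround and that "the impact of study procedures on clinic flow will be minimal". Table 7 gives the target as "10 visits per clinic per observation period" and the analysis as rank-sum tests and flow analysis.

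The article describes the timing of the observations in different ways:

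- Description of the Protocol for the GAIN Study: observations were made "at one time point preimplementation and 2 time points postimplementation".
- GAIN Time and Motion Observations: the March-April 2023 round took place "during a regulatory study pause in enrollment". Only the round from November 2023 to October 2024 is assigned to assessing the effect of the POC NAT on clinic flow.
- Table 6 agrees with the latter. Its title is "Total time observed in clinic (minutes), including waiting room time, during 1 observation period preenrollment (2021) and 1 period while enrollment was paused (2023").

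On who is observed, Time and Motion Eligibility says: "Any Madison Clinic or MOD Clinic patient was eligible to be observed by study staff". Table 1 lists both nonparticipants and Madison participants with HIV as sources of these data.

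**The concern.** A power of 80% has meaning only for a named difference. The article lists every other input and leaves that one out, so a reader cannot tell what 20 visits per period were meant to detect. The 50% SAMBA share is attached to each period, although no one could have been randomized to SAMBA in two of the three.

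The hypothesis and the test also point in different directions. The hypothesis is that impact is small. A rank-sum test looks for a difference, and with few visits it will often find none whether or not one exists. No margin defines how small counts as minimal. If the plan is followed as written, a non-significant result can stand as evidence of minimal impact while delays that matter in a visit of about an hour remain compatible with the data. Clinic flow is a central feasibility question here, because the test takes up to 120 minutes and the median visits observed were 73 and 64 minutes.

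**Working it through.** **Inputs.** From the sample-size sentence: 20 per period, 50% SAMBA (so 10 versus 10), mean 66, SD 29, alpha .05, power 80%. From Table 6: total SD 31.6 in 2023 (n = 22) and 55.0 in 2021 (n = 25). Sidedness is not stated, so two-sided is assumed.

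**1. Can 20 be reproduced?** Not directly, since no difference is given. One candidate is the gap between turnaround and mean visit, 120 − 66 = 54 minutes. Per arm that needs 2 × (1.960 + 0.842)² × (29/54)² ≈ 4.5, so 5 per arm or 10 in all. That does not lead to 20, and the figure can be neither confirmed nor refuted.

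**2. What 10 versus 10 detects.** Solve for the difference instead.

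- Normal approximation: 29 × √(1/10 + 1/10) × (1.960 + 0.842) = 36.3 minutes.
- Exact two-sided t-test: 38.4 minutes, and 38.4/66 = 58% of the assumed mean visit.
- Rank-sum test, using its relative efficiency of 0.955 under normality: 38.4/√0.955 = 39.3 minutes. Simulation with normal data gives 76% power at 38.4 minutes and 79% at 40.
- At the 2023 SD of 31.6 (t-test): 41.9 minutes.
- One-sided t-test at SD 29: 33.5 minutes.

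**3. Power for smaller delays (t-test, 10 versus 10).**

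| Delay | SD 29 | SD 31.6 |
|---|---|---|
| 10 min | 11% | 10% |
| 15 min | 20% | 17% |
| 20 min | 31% | 27% |
| 30 min | 59% | 52% |

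**4. Precision.** The 95% half-width is t(18) × SD × √0.2 = 2.101 × 29 × 0.447 = 27.2 minutes, or 29.7 at SD 31.6. An observed difference of exactly zero would still leave delays of up to 27 minutes inside the interval.

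**5. Comparison across periods.** At SD 29 the t-test with 80% power detects 26.4 minutes for 20 versus 20, and 22.0 minutes for 20 versus the 25 + 22 = 47 earlier visits. As shares of the 66-minute visit these are 40% and 33%.

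**6. What a margin would need.** If the true difference is zero, excluding a margin m with 80% power (one-sided .025, SD 29) takes 2 × (1.960 + 0.842)² × (29/m)² per arm: 133 for 10 minutes, 59 for 15, 34 for 20 and 15 for 30. The article states no margin, so these values of m are illustrative.

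**7. The periods side by side.**

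| Period | Enrollment status | Could 50% be randomized to SAMBA? |
|---|---|---|
| Feb-Jul 2021 | Before enrollment | No |
| Mar-Apr 2023 | Paused | No |
| Nov 2023-Oct 2024 | Open | Yes, among trial participants only |

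Because any clinic patient may be observed, even the third period does not guarantee 10 versus 10.

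**The case against.** No arithmetic error is shown. The 38 minutes is a back-calculation, and a condensed article may leave its target difference to a fuller protocol. That stands, so the omission alone would be a reporting point. What goes beyond it is that the 50% share is applied to periods that cannot have it, and that a difference test is paired with a hypothesis of little difference.

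Four stronger readings are tempting, and the documents do not support them.

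- **The planning SD is badly wrong.** A reader might take the 2021 SD of 55.0 and conclude that only a 73-minute difference is detectable, with 12% power for 20 minutes. That SD rests largely on one visit of 301 minutes. Removing it from n = 25, mean 80.7 and SD 55.0 leaves a mean of 71.5 and an SD of 31.0. Those figures also assume a t-test, while the plan is a rank-sum test, which is much less sensitive to one extreme value. In a simulation with SD 31 and an assumed 1 visit in 25 at 301 minutes, its power at 73 minutes was about 96%. The 2023 SD of 31.6 is only 9% above 29. Madison Clinic visits alone, both periods combined, give a mean of 66.05 and an SD of 27.7, close to the planning values.
- **A half-hour delay would usually be missed.** At SD 29 its power is 59%, so it would more often be found than missed. The statement holds for 20 minutes.
- **The 2023 pause data will dilute the effect.** The postimplementation label is loose, but no text plans to pool those visits with the third period, and the methods assign only the third period to assessing impact.
- **SAMBA versus no SAMBA settles the hypothesis.** The hypothesis concerns study procedures. Both trial arms share consent paperwork, surveys and, from April 2023, venipuncture, so that contrast isolates only the SAMBA part.

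The article also plans flow analysis and records research-procedure time directly in the final dataset. That is useful descriptive evidence, but it does not make a non-significant rank-sum test informative about small effects.

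**Conclusion.** The point holds in a limited form. The 80% power statement can describe only the third period, where 10 versus 10 visits reach that power for roughly 38 to 40 minutes at SD 29, or about 42 minutes at the 2023 SD (t-test). A rank-sum test of this size cannot support a claim of minimal impact, and comparison with earlier periods improves the detectable difference without changing that conclusion.

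This rests on an equal split of 20 visits, a two-sided 5% level, and roughly normal visit times with the stated SD. The third-period sample size actually reached is not reported, so the realized precision may differ. The companion hypothesis, that visits average under 120 minutes, is not affected: a one-sample t-test with n = 20 and SD 29 has 80% power for about 19 minutes, against an assumed gap of 54. This is a secondary component, and the remedy should be made before its final results are reported.

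**What to change.** 1. Restate the power sentence as applying to the third period only. Give the detectable difference: about 38 to 40 minutes at SD 29, and about 42 at SD 31.6.
2. Report the estimated difference in visit time with a 95% confidence interval for two contrasts: SAMBA versus no SAMBA within the third period, and the third period versus the two earlier no-SAMBA periods. The second bears on procedures shared by both arms. It is not randomized and should be labelled so. Present the recorded research-procedure time alongside.
3. State a margin for minimal impact before the final dataset is analyzed, and make the claim only if the interval excludes it. Otherwise present the component as descriptive.
4. Reconcile the count of two postimplementation time points in the protocol description with the enrollment pause stated in the time-and-motion methods and in Table 6.

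The cost is a few sentences and two confidence intervals. No new data are needed, and the claim becomes more modest.
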